## Clinical Efficacy Analysis

- Use FAS Analysis:
- Objective Response Rate (ORR): Calculate the ORR and its 95% confidence interval.
- Disease Control Rate (DCR): Calculate the DCR and its 95% confidence interval.
- Progression-Free Survival (PFS): The time from the start of the study to the date of the first recorded progression (PD) or death, whichever occurs first; if no disease progression is observed, the cutoff date should be the date of the last tumor measurement. PFS will be summarized using Kaplan-Meier plots, and the rates of censoring, quartiles, and their 95% confidence intervals will be listed, along with estimates of progression-free survival rates at different time points and their 95% confidence intervals.

## Efficacy Endpoint Analysis

Using the baseline at 0.5 hours before administration, the time-dependent changes in histone acetylation levels will be described for each dose group at various time points.

Exploratory analyses will be tentatively conducted to assess the relationships between pharmacodynamic (PD) endpoints and drug exposure, as well as between PD endpoints and efficacy. This includes examining the relationship between blood drug concentration and changes in pharmacodynamic values, the relationship between maximum PD changes, area under the curve (AUC), and dose, as well as the relationship between maximum PD changes, AUC, and efficacy.

## Statistical Software

Pharmacokinetic (PK) parameters will be calculated using WinNonlin (version 8.1 or higher), while other analyses will be conducted using SAS software (version 9.4 or higher).

Detailed statistical methods will be provided in the statistical analysis plan.

## Interim analysis

This study will not conduct an interim analysis.

# Trail management

## Modifications to the Study Protocol

Neither the investigator nor the sponsor may modify the study protocol without the consent of the other party. Any modifications to the protocol that could affect the conduct of the study, patient benefits, study objectives, study design, sample size, or study procedures must be presented in a protocol amendment. These amendments must be approved by the sponsor, the investigator, and the ethics committee before they can be implemented.

## Completion of the Electronic Case Report Form (eCRF)

The investigator will first summarize the general information about the subjects according to the content of the "Screening Form" to determine whether the subjects are eligible for enrollment. After enrollment, treatment and assessments will be conducted as required by the protocol, and relevant information will be recorded in the hospital medical records or original data. Subsequently, the data required by the protocol, including hospital records and test results, will be entered into the eCRF.

During the study, the Clinical Research Associate (CRA) will perform source data verification (SDV) comparing the original data with the data in the Electronic Data Capture (EDC) system. Any data that significantly deviates from clinically acceptable ranges must be verified and explained. Suspect data will prompt online queries, which the investigator or Clinical Research Coordinator (CRC) will verify against the original data and make corrections in the EDC. Throughout the study, the investigator should allow the sponsor’s monitors or representatives to inspect study-related documents at the research site (such as patient informed consent forms, study drug accountability logs, and ethics committee approval documents). When monitors visit, they will conduct a thorough review of patient records to verify the information recorded in the hospital medical records or eCRF, particularly key information related to safety and efficacy.

## Data Quality Assurance

To ensure the integrity, accuracy, and reliability of the data, the following measures have been implemented in this study:

1. Selection of qualified and experienced research institutions and investigators;
2. Providing detailed information about the study protocol to investigators through lectures and written materials before the study begins, and collaboratively developing solutions for potential issues;
3. Regular verification of the authenticity, accuracy, and completeness of the data by monitors, data managers, and other personnel;
4. If any data discrepancies are identified, timely communication with the investigators should occur for confirmation or correction.

## Record Retention

The research institution will retain the hospital medical records and other original data for each subject. After the study concludes, the data management team will export the finalized eCRF data from the Electronic Data Capture (EDC) system and transfer it to the sponsor. All records will be maintained for a minimum of five years after the completion of the clinical trial.

## Monitoring

Throughout the clinical trial, the Contract Research Organization (CRO) for this project will designate qualified monitors to conduct regular on-site monitoring of the clinical trial centers to ensure strict compliance with all aspects of the study protocol. The trial centers should assist and cooperate with the monitors in their work.

The main tasks of the monitoring process include:

1. Confirm that the trial site has appropriate conditions before the clinical trial begins, including personnel staffing and training, laboratory equipment that is complete and operational, all necessary testing conditions related to the trial, familiarity with the requirements of the study protocol, and sufficient numbers of researchers participating in the study.
2. Monitor the investigator's adherence to the study protocol during the trial, ensuring that informed consent has been obtained from all subjects prior to their enrollment, understanding the subjects' enrollment rates and the progress of the trial, and confirming the eligibility of enrolled subjects.
3. Ensure that all data is recorded and reported accurately and completely, with all electronic case report forms entered correctly and consistent with the original data. Any errors or omissions should be corrected or noted. Changes in dosage, treatment modifications, concomitant medications, adverse events, lost to follow-up, and missed assessments for each subject must be confirmed and recorded. Verify that the reasons for withdrawal or loss to follow-up for enrolled subjects are documented in the electronic case report forms.
4. Confirm that all adverse events are recorded, serious adverse events are reported and documented within the specified time frame; verify that trial medications are supplied, stored, distributed, and retrieved in accordance with relevant regulations, with appropriate records maintained.
5. Assist the investigator with necessary notifications and applications, and report trial data and results to the sponsor.
6. Clearly and accurately document any follow-ups that the investigator failed to perform, any tests that were not conducted, any assessments that were not completed, and whether any errors or omissions were corrected.
7. Complete a written monitoring report after each visit, including the date and time of the monitoring visit, the name of the monitor, and the results of the monitoring.

## Audits and Inspections

Throughout the clinical trial process or after its completion, the sponsor, Chengdu Zenitar Biomedical Technology Co., Ltd, the CRO, government regulatory authorities, and independent ethics committees have the right to conduct audits or inspections at the trial centers, which must cooperate with these activities.

The main tasks of the audits include: ensuring the existence of all documentation required by Good Clinical Practice (GCP); verifying original data against eCRF data; inspecting instruments and equipment; reviewing the storage and management of trial medications; and assessing the fulfillment of the monitor's responsibilities, among other tasks.

## Study Completion/Termination

### Study Completion

The study is considered complete after the last participant's follow-up has concluded, at which point the investigator should notify the sponsor.

### Study Termination

Study termination refers to the premature cessation of the clinical trial before it is completed according to the protocol. The primary purpose of terminating a study is to protect the rights of participants, ensure the quality of the trial, and avoid unnecessary economic loss. All parties involved in the study should be promptly notified of an early termination. Reasons for terminating the study include, but are not limited to:

1. Significant errors are found in the clinical trial protocol that make it difficult to assess the safety of the drug;
2. Concerns related to safety;
3. The sponsor requests termination (e.g., for reasons related to funding, management, etc.);
4. The National Medical Products Administration or ethics committee mandates the termination of the study for any reason.。

## Use and Publication of Information

All information and data related to this trial are confidential and are the property of the sponsor. Except as required by the National Medical Products Administration, the investigator may not disclose any information to third parties in any form without the written consent of the sponsor, nor may this information be used for any other purposes.

The investigator is required to provide all data obtained during the trial to the sponsor. For the protection of legitimate business secrets, the investigator may not publish research results without prior review and approval from the sponsor.

## Responsibilities of All Parties

The investigator must read and understand the content of the study protocol in detail and execute the trial in strict accordance with the "Good Clinical Practice" (GCP) guidelines and the protocol. They are responsible for recording the participants' original data, obtaining informed consent, promptly entering data into the electronic case report forms, and documenting and counting the investigational medication. The investigator should accept regular monitoring by the monitors to ensure the quality of the clinical trial and ensure that participants receive appropriate treatment in the event of adverse events during the trial. After the clinical trial concludes, the investigator should review and finalize the summary report, sign it, and date it.

The sponsor is responsible for initiating the clinical trial and providing funding. The Contract Research Organization (CRO) collaborates with the sponsor to organize, monitor, and audit the clinical trial. The sponsor is also responsible for providing the investigational drug to the investigator and ensuring its quality. Additionally, the sponsor is responsible for submitting the trial summary report to the National Medical Products Administration.

# Ethical Principles

## Responsibilities of the Investigator

The investigator is responsible for ensuring compliance with the Declaration of Helsinki and the Chinese Good Clinical Practice (GCP) guidelines, as well as relevant laws and regulations, while executing this study protocol.

## Approval of the Ethics Committee

Before the trial begins, the investigator must provide relevant materials as required by the ethics committee to obtain their approval.

This trial may only commence after receiving written approval from the ethics committee. If the study protocol needs to be revised during the course of the research, the revised protocol must be submitted to the ethics committee of the sponsoring institution for filing/approval before implementation. If important new information regarding the investigational drug is discovered, the relevant materials must be modified in writing and submitted to the ethics committee for approval, and informed consent from the participants must be obtained again. At the conclusion of the trial, the investigator should notify the ethics committee that the trial is completed.

## Informed Consent

Before enrolling in the trial, the investigator should provide the participant or their legal representative with a complete and thorough explanation of the purpose, methods, procedures, potential benefits, and possible risks of the trial, and this information should be documented in writing. Only after obtaining the participant's consent and voluntarily signing the informed consent form can they be enrolled in the clinical trial. The participant retains a copy of the informed consent form.

- Information to be Provided to Participants

1. Participation in the trial is voluntary, and participants have the right to withdraw from the trial at any stage without discrimination or retaliation, and their medical treatment and rights will not be affected.
2. The personal information of participants in the trial is confidential. Only the regulatory authorities, ethics committee, or sponsor may access the data of participants when necessary.
3. Participants will be informed about the purpose of the trial, the methods, procedures, and duration, as well as the expected potential benefits and risks.
4. In the event of any trial-related harm, participants may receive appropriate treatment and compensation.

- Important Considerations for Signing the Informed Consent Form

1. The investigator must provide a thorough and detailed explanation of the trial to the participant and allow sufficient time for the participant to consider whether they wish to participate in the study. The informed consent form should only be signed after obtaining the participant's full consent.
2. The informed consent form must be signed and dated by the participant or their legal representative. The investigator or their representative who conducts the informed consent process must also sign and date the form.
3. The informed consent process should be conducted in a language and manner that the participant or their legal representative can understand. Throughout the trial, the participant has the right to access any information or materials related to the study at any time.
4. If the participant or their legal representative is unable to read, a witness must be present throughout the process. After the informed consent form is explained in detail, the participant or their legal representative may provide verbal consent, which must be signed and dated by the witness.
5. For participants who are legally incompetent, if the ethics committee gives its principal approval and the investigator believes that participation in the clinical trial is in the participant's best interest, these patients may also be included in the study, provided their legal representative signs and dates the consent form.
6. If the informed consent form is not signed by the participant, legal representative, or witness, the investigator must document the situation and the reasons for the inability to obtain consent, and sign this record.

# Appendix

## ECOG Performance Status Scoring Criteria

| **Grading** | **Performance Status** |
| --- | --- |
| 0 | Fully active, able to carry on all normal activities without restriction. |
| 1 | Restricted in physically strenuous activity but ambulatory and able to carry out work of a light or sedentary nature. For example, light housework, office work. |
| 2 | Ambulatory and capable of all self care but unable to carry out any work activities. Up and about more than 50% of waking hours. |
| 3 | Ambulatory and capable of all self care but unable to carry out any work activities. Up and about more than 50% of waking hours. |
| 4 | Completely disabled. Cannot carry on any self-care. Totally confined to bed or chair |
| 5 | Death. |

## New York Heart Association (NYHA) Functional Classification

Class I: Patients have heart disease but do not experience any limitations in physical activity. Ordinary physical activities do not cause fatigue, palpitations, shortness of breath, or angina.

Class II: Patients with heart disease have mild limitations in physical activity. They do not experience any symptoms at rest, but ordinary physical activities may lead to fatigue, palpitations, shortness of breath, or angina.

Class III: Patients with heart disease have marked limitations in physical activity. Symptoms occur with less than ordinary physical activity.

Class IV: Patients with heart disease are unable to engage in any physical activity. Symptoms of heart failure occur even at rest and are exacerbated by physical activity.

## Criteria for Mild Abnormal Laboratory Values

**Criteria for Mild Abnormal Laboratory Values - NCI CTCAE v5.0 Grade 1**

| Laboratory Test Item | Mildly Abnormal Criteria | Laboratory Test Item | Mildly Abnormal Criteria |
| --- | --- | --- | --- |
| Hb | < LLN - 100 g/L | Cr | > ULN – 1.5×ULN |
| WBC | < LLN - 3000/mm^3^ | Na | > ULN – 150 mmol/L  < LLN – 130 mmol/L |
| N | < LLN - 1500/mm^3^ | K | > ULN – 5.5 mmol/L  < LLN – 3.0 mmol/L |
| L | < LLN - 800/mm^3^ | Ca | > ULN – 2.9 mmol/L  < LLN – 2.0 mmol/L |
| Plt | < LLN - 75000/mm^3^ | Mg | > ULN – 1.23 mmol/L  < LLN – 0.5 mmol/L |
| BIL | > ULN - 1.5×ULN | P | < LLN – 0.8 mmol/L |
| ALT | > ULN - 2.5×ULN | Glu | > ULN – 8.9 mmol/L  < LLN – 3.0 mmol/L |
| AST | > ULN - 2.5×ULN | TG | > ULN – 2.5×ULN |
| ALP | > ULN - 2.5×ULN | CHOL | > ULN – 7.75 mmol/L |
| CPK | > ULN - 2.5×ULN | CK-MB | > ULN |
| LDH | > ULN - 2.5×ULN | Troponin I | > ULN |
| α-HDBD | > ULN - 2.5×ULN | CRP | > ULN |

## Criteria for the Evaluation of Multiple Myeloma

"Chinese Guidelines for the Diagnosis and Treatment of Multiple Myeloma (Revised in 2017)" and the 2016 International Myeloma Working Group (IMWG)

| **IMWG Response Criteria** | |
| --- | --- |
| **sCR** | The following definition of complete response includes a normal free light chain (FLC) ratio, and a bone marrow biopsy (after calculating ≥100 plasma cells) showing no clonal cells based on immunohistochemical examination (with κ and λ ratios of ≤4:1 or ≥1:2 for the patient). |
| **CR** | Serum and urine immunofixation electrophoresis negative, with no evidence of any soft tissue plasmacytomas, and plasma cells in the bone marrow aspirate <5%. |
| **VGPR** | Immunofixation electrophoresis may detect serum and urine M proteins, but electrophoresis is negative or serum M protein is reduced by ≥90% with urine M protein levels. |
| **PR** | - Serum M protein decreased by ≥50% and 24-hour urine M protein decreased by ≥90% or reached <200 mg/24 h. - If serum and urine M protein cannot be measured, a difference of ≥50% in free light chain (FLC) levels between the affected and unaffected areas can be used as a substitute for the M protein criteria. - If serum and urine M protein testing and serum free light chain testing cannot be performed, plasma cells must be reduced by ≥50% to substitute for the M protein criteria, provided that the baseline percentage of plasma cells in the bone marrow is ≥30%. In addition to these criteria, if present at baseline, the size of soft tissue plasmacytomas (the sum of the products of the maximum vertical diameters of multiple measurable lesions [SPD]) must decrease by ≥50%. |
| **MR** | Serum M protein decreased by ≥25% but ≤49%, and 24-hour urine M protein decreased by 50%-89%. In addition to the criteria listed above, if present at baseline, the size of soft tissue plasmacytomas (SPD) must decrease by ≥50%. |
| **SD** | It is not recommended to use this as a response indicator; the best description of disease stability should be "time to progression estimate." This does not meet the criteria for CR, VGPR, PR, MR, or PD. |
| **PD** | Meets any one or more of the following criteria:  Any one or more of the following criteria indicate a minimum confirmation of response value increase of 25%.   - Serum M protein (the absolute increase must be > 0.5 g/dL); - If the baseline minimum M component value is ≥5 g/dL, an increase in serum M protein of ≥1 g/dL; - Urine M protein (the absolute increase must be ≥200 mg/24 h); - For patients where serum and urine M protein levels cannot be measured, the difference in free light chain (FLC) levels between the affected and unaffected areas (the absolute increase must be >10 mg/dL); - For patients where serum and urine M protein levels cannot be measured and where the FLC levels in the affected area cannot be measured, the percentage of plasma cells in the bone marrow is not affected by baseline status (the absolute increase must be ≥10%); - New lesions appear, with the SPD of >1 lesion increasing by ≥50% from the lowest value, or the maximum diameter of the original lesion with a minimum diameter >1 cm increasing by ≥50%; if this is the only measurable value of the disease, the number of circulating plasma cells (at least 200 cells per μL) increases by ≥50%. |
| **Clinical relapse** | Clinical relapse requires one or more of the following criteria:   - Direct indicators of disease progression and/or end-organ dysfunction (such as elevated calcium levels, renal failure, anemia, and osteolytic lesions [CRAB symptoms]) associated with potential clonal plasma cell proliferation. This is not used to calculate time to progression or progression-free survival but can be selectively reported or used in clinical practice; - The occurrence of new soft tissue plasmacytomas or bone lesions (osteoporotic fractures do not constitute lesions); - A clear increase in the size of existing plasmacytomas or bone lesions. A clear increase is defined as a ≥50% increase in the SPD of measurable lesions (and ≥1 cm) after consecutive measurements; - Hypercalcemia (>11 mg/dL); - Hemoglobin decrease of ≥2 g/dL unrelated to treatment or other non-myeloma related symptoms; - An increase in serum creatinine of 2 mg/dL or more at the start of autonomous treatment, attributed to myeloma; - Hyperviscosity related to serum paraproteins. |
| **Relapse after complete response (used only when the endpoint of the study is disease-free survival)** | Meets any one or more of the following criteria:   - Immunofixation or electrophoresis shows reappearance of serum or urine M protein; - Development of bone marrow plasma cells ≥5%; - Appearance of any other progression markers (such as new plasmacytomas, osteolytic lesions, or hypercalcemia) (as mentioned above). |

*Note: CR = Complete Response, sCR = Strict Complete Response, PR = Partial Response, VGPR = Very Good Partial Response, MR = Minimal Response, SD = Stable Disease, PD = Progressive Disease.*

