| **Drug Administration Plan** | The dosing phase of this study includes three stages: the single-dose phase, the multiple-dose phase, and the extended dosing phase. The pharmacokinetics of the single-dose and multiple-dose administrations are combined, during which safety, tolerability, and preliminary efficacy are observed.  **1. Single-Dose Phase**  The single-dose escalation phase will begin with the starting dose and proceed in an ascending order from low to high doses, with 3 to 6 subjects enrolled in each dose group. In each dose group, 3 subjects will be enrolled sequentially, and a single dose will be administered on Day 1 (D1) at that dose, followed by a 6-day observation period (D2-D7). Each subject will receive treatment with a single dose.  **2. Multiple-Dose Phase**  After completing the pharmacokinetic blood sampling for the single-dose administration, if the subject is well-tolerated, they will enter the multiple-dose phase, with doses administered on Days 8, 11, and 15. Each subject will receive the same dose as in the single-dose phase, with the dose-limiting toxicity (DLT) observation period defined as the first administration to 25 days after the first dose. Initially, only one subject will be enrolled in each dose group to observe their tolerability and safety within the 25 days following the first dose. Only if this subject does not experience a DLT will the remaining two subjects in the same dose group be allowed to enroll simultaneously.  If none of the 3 subjects in a dose group experience DLT, the trial will proceed to the next dose group. If 1 out of the 3 subjects in a dose group experiences DLT, an additional 3 subjects will be recruited to receive the same dose of the investigational drug, and they will be monitored for DLT occurrence.  If 1 DLT occurs among the 6 subjects, the trial will proceed to the next dose group. If 2 or more DLTs occur among the 3 subjects, or if 2 or more DLTs occur among the 6 subjects, the trial will be reduced to the previous dose group. If the previous dose group has fewer than 6 evaluable subjects, an additional 3 subjects will be enrolled to bring the total number of evaluable subjects to 6. If no more than 1 DLT occurs among the 6 evaluable subjects, the trial will be halted, and that dose group will be declared as the maximum tolerated dose (MTD). If the previous dose group has already reached 6 evaluable subjects, the trial will be halted, and that dose will be declared as the MTD.  During the multiple-dose escalation trial, real-time analysis of the pharmacokinetic (PK) data for the selected dose groups will be conducted to determine whether the drug reaches a saturation state in the body based on PK and pharmacodynamic (PD) indicators.  **3. Extended Treatment Phase**  After completing the single-dose and multiple-dose phases, if the efficacy assessment indicates clinical benefit for the subject, they will enter the extended dosing phase. In the extended dosing phase, treatment may continue according to the original dosing regimen or with adjustments to the dose based on the subject's tolerability and existing clinical results. Each dosing cycle lasts 21 days, with doses administered on Days 1, 4, 8, and 11 of each cycle. The number of extended dosing cycles will vary based on the patient's efficacy; subjects who achieve an objective response rate of partial response (PR) or higher after 6 cycles may continue receiving the treatment until disease progression, while those who do not reach PR will discontinue the treatment. Efficacy and safety data will continue to be collected during the extended dosing phase. |

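### Section 14.4 gives no rule for myeloma measurable in only serum or only urine: read literally, urine-only disease cannot be PR or MR, and serum-only disease cannot be MR

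*Protocol*

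**What the plan says.** All of the following is in the Protocol.

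- **PR (section 14.4).** The first item is "Serum M protein decreased by ≥50% and 24-hour urine M protein decreased by ≥90% or reached <200 mg/24 h". A free-light-chain substitute opens with "If serum and urine M protein cannot be measured". A plasma-cell substitute reads "If serum and urine M protein testing and serum free light chain testing cannot be performed, plasma cells must be reduced by ≥50" per cent, with a further condition on baseline marrow.
- **MR (14.4).** "Serum M protein decreased by ≥25% but ≤49%, and 24-hour urine M protein decreased by 50%-89" per cent. MR has no alternative urine level and no substitute.
- **VGPR (14.4).** Immunofixation may still detect M protein, but "electrophoresis is negative or serum M protein is reduced by ≥90% with urine M protein levels". The last phrase has no threshold.
- **SD (14.4).** The residual category: whatever is not CR, VGPR, PR, MR or PD.
- **PD (14.4).** Any one of a list of items suffices. Serum and urine M protein are separate items, each with its own absolute increase.
- **ORR (section 7.5 and the note to 14.4).** For myeloma, sCR, CR, VGPR, PR and MR count as response; SD does not. Section 10.6 reports ORR with a 95% confidence interval.
- **Treatment after six extension cycles (Synopsis, Drug Administration Plan).** Subjects at PR or better may continue, "while those who do not reach PR will discontinue the treatment".
- **Tests.** The M-protein panel (flowchart notes; sections 6.1, 6.3 and 6.5) lists serum protein electrophoresis, immunofixation, β2-microglobulin and serum immunoglobulins with light chains. The listed urine test is routine urinalysis.

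**The concern.** M protein may be measurable in serum, in urine or in both. A rule that joins a serum condition and a urine condition with *and* works only if it also says what happens when one of them has no baseline value. Section 14.4 does not say. A compartment with nothing to measure cannot fall by a stated percentage, so the joint condition fails however well the other compartment responds.

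Two things are at stake. An intermediate response in single-compartment disease is scored SD and counted as a non-response in ORR, while progression in the same subject can be declared on that one compartment. And for urine-only disease, PR is also the test used after cycle 6, so the classification has a use beyond the efficacy table.

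**Working it through.** The plan states no figure to reproduce. The check applies the PR and MR rows literally; VGPR, CR and PD were left out of the coding and are discussed separately.

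**Inputs, from 14.4**
- PR: serum fall ≥50% *and* (urine fall ≥90% *or* urine <200 mg/24 h).
- MR: serum fall 25–49% *and* urine fall 50–89%.
- SD: the remainder, PD aside.

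Falls ran from 0 to 100% in 1-point steps, giving 101 values. Baseline urine levels of 500, 1000, 2000 and 5000 mg/24 h are assumptions.

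**Step 1: urine-only disease, 4 × 101 = 404 profiles.** There is no serum M protein to fall, so the serum condition fails in both rows: PR or MR in 0 of 404. The light-chain substitute requires serum and urine both to be unmeasurable, and here urine is measurable. The plasma-cell substitute requires light-chain testing to be unavailable as well. VGPR's numeric route is again a serum fall, which leaves VGPR by negative electrophoresis, or CR.

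**Step 2: serum-only disease, 101 profiles.** Urine M protein is below 200 mg/24 h throughout, so the urine part of PR is met without any urine fall. PR is reached at every serum fall of 50–100%: 51 of 101. MR needs a 50–89% urine fall that cannot occur: 0 of 101. The 25 profiles with a 25–49% serum fall become SD.

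**Step 3: could *or* be read differently?** Take PR as (serum ≥50% and urine ≥90%) *or* urine <200 mg/24 h. Urine-only disease then reaches PR once the level drops below 200. The number of profiles from baselines 500, 1000, 2000 and 5000 is 40 + 20 + 10 + 4 = 74 of 404. But every serum-only subject becomes PR, including one with no fall at all: 101 of 101. That reading cannot be intended.

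**Step 4: example subjects, literal rule against a measurability clause**

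| Subject | As written | With clause |
|---|---|---|
| Urine only, 2000 to 100 mg/24 h (−95%) | SD | PR |
| Urine only, 3000 to 240 mg/24 h (−92%) | SD | PR |
| Urine only, −60% from 2000 mg/24 h | SD | MR |
| Serum only, −35% | SD | MR |
| Serum only, −60% | PR | PR |
| Both, serum −35%, urine −70% | MR | MR |

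The urine-only rows assume that electrophoresis is still positive.

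**Step 5: both compartments measurable but discordant.** Take serum −60% with urine 2000 mg/24 h −70%, which leaves 2000 × 0.30 = 600 mg/24 h. PR fails on urine (−70% is short of 90%, and 600 is above 200). MR fails because 60% exceeds its 49% serum ceiling. The result is SD. A measurability clause alone does not change this.

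**Step 6: can the urine conditions be scored?** None of the listed M-protein tests is a 24-hour urine M-protein quantification. From the listed tests, the urine parts of PR and MR cannot be scored for any myeloma subject.

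**The case against.** The strongest reply is that the table is a condensed, translated version of criteria it attributes to the IMWG and a Chinese guideline. It already turns on measurability in the PR substitutes and in PD, so an experienced assessor would treat a condition with no baseline component as not applicable. That may happen, but the table does not say it. The substitutes cover only the case where both compartments are missing, and PD shows that the protocol separates serum and urine when it means to. Whether the table departs from its cited sources cannot be judged from the protocol, so a transcription error is not claimed.

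A reader might also infer more than the text supports:

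- **That PR always needs a fall in both compartments.** It does not. The level below 200 mg/24 h satisfies the urine part, so serum-only subjects can be PR.
- **That real responses in general are lost.** VGPR by negative electrophoresis and CR remain open and count in ORR. Only intermediate responses are affected.
- **That one missed responder moves a group's ORR by 17 points (1/6) or 33 points (1/3).** This assumes ORR by dose group and a single-compartment myeloma subject in that group. Section 10.6 does not specify ORR by dose group, dose groups mix diseases, and there is no myeloma quota.
- **That the MR gap affects continuation.** The test after cycle 6 is PR or better, so MR and SD are treated alike there.

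The consequence is limited, as the objection says: efficacy is a preliminary secondary aim, the analysis is descriptive, and DLT and MTD decisions do not use myeloma response.

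**Conclusion.** The point holds in limited form. Under the only workable reading of 14.4, urine-only disease cannot be PR or MR, and serum-only disease cannot be MR. Such subjects are scored SD unless they reach VGPR or CR, or progress. Any resulting error in myeloma ORR from this gap is downward. For urine-only disease short of VGPR, it also decides the outcome of the PR test after cycle 6; no view is taken here on that treatment rule.

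The size is unknown: the number of myeloma subjects and the share with single-compartment disease are not stated, and the share could be zero. For scale only, if ORR were taken over all 21 to 42 planned subjects, one missed responder would be 1/42 to 1/21, about 2 to 5 percentage points. The conclusion assumes that the table is applied as worded. It merits correction because these response rules are fixed in the protocol, but it touches only a secondary, descriptive endpoint.

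**What to change.** 1. Add to 14.4, for VGPR, PR and MR: the serum condition applies only if serum M protein, and the urine condition only if urine M protein, was measurable at baseline. If one was not measurable, response is scored on the other, provided the first does not meet PD. State the measurability limits used.
2. State how a subject measurable in both compartments is scored when the two fall in different categories, such as serum −60% with urine −70%.
3. Reconcile the M-protein tests in the flowchart notes and sections 6.1, 6.3 and 6.5 with the urine criteria, so that every condition in 14.4 can be scored from scheduled data.

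The cost is a few sentences in the appendix, a baseline measurability flag, and a 24-hour urine M-protein measurement for myeloma subjects. The criteria already presuppose that measurement, but it is an addition to the listed tests, so the change is more than wording.
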